### Patient dropout and protocol violations

Patients who drop out of the trial will be recorded and the reason for dropout will be noted. The principal investigator will record and report any protocol violations.

### Side effects and adverse events reporting

The department routinely uses both types of shoulder prostheses. The treatments’ risks and disadvantages are therefore not expected to differ from normal patient application outside the trial. They include superficial infection, deep infection, loosening of the prosthesis, nerve or vascular injury during surgery, lack of healing, and prosthesis migration. The amount of ionizing radiation to which the patients are exposed during the CT scan and X-rays does not differ from that for patients outside the study.

To assess possible complications after prosthesis insertion, we will record any case of deep infection, nerve injury, implant loosening (based on radiographic images), heterotopic ossification, instability, dislocation, implant removal, and revision surgery or any adverse event that leads to hospitalization one year after surgery. All complications will be reviewed at the end of the trial and reported.

## Statistical analysis plan

### Sample size and power calculation

No existing studies report the minimal clinically important difference (MCID) of WOOS, but the MCID of the OSS was investigated and found to be 6 points or 12.5% of a maximum score [26]. By extrapolating MICD from OSS to WOOS, based on the known MCID for OSS, we estimated the accepted clinically meaningful change (ACMC) of WOOS to 237.5 points (12.5%).

With an ACMC of 12.5% and a standard deviation (SD) of ±20.0, which we found from our retrospective evaluation of patients operated with stemless TSA in our department, we need to include 64 patients, 32 in each group, to be 80% sure that the lower limit of a one-sided 95% confidence interval will be above the non-inferiority threshold of – 12.5%. With a loss of follow-up assumption of 20%, a total of 78 patients is required [27].

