**Materials and methods:**

A randomized clinical trial will be conducted. Eighty patients with clinical and radiological signs of primary or post-traumatic glenohumeral osteoarthritis, computed tomography (CT) scan-verified adequate glenoid bone stock, and no total rupture of rotator cuff tendons verified by a magnetic resonance imaging (MRI) scan will be randomly allocated to a stemless or stemmed TSA. The primary outcome will be the Western Ontario Osteoarthritis Shoulder (WOOS) score at 12 months. Secondary outcomes are the WOOS score at three months and the Oxford Shoulder Score (OSS) and EQ-5D at 3 and 12 months. All complications, including glenoid and humeral component loosening, instability, rotator cuff tear, intraoperative and postoperative periprosthetic fracture, nerve injury, infection, deltoid injury, and symptomatic deep venous thrombosis, will be reported.

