## Methods/Design

### Study design

An investigator-initiated, blinded (patient and data analyzer), non-inferiority, randomized controlled clinical trial.

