### Material

Seventy-eight patients with shoulder osteoarthritis randomized to either stemmed or stemless shoulder prosthesis. The flow of participants into the study are demonstrated in Fig. 1

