## Discussion

Through randomization and blinding, we aim to decrease the risk of bias. The use of usual care increases the study’s validity and the results can be generalized for the rest of this patient population. The current study will provide high-quality evidence regarding the short-term patient-reported outcome of stemless and stemmed TSA. We will attempt to avoid the type-II error (when hypothesis testing does not reject the null hypothesis, even though the null should have been rejected) by using a proper sample and by adding 20% to the sample size compensating for dropouts. However, we will reduce dropout bias by obtaining permission (at the first visit) to call patients who do not show up for subsequent visits. We will avoid selection bias through randomization and reduce interviewer bias by letting patients answer the questionnaires without interference from the medical staff and hand it back to the receptionist, who will check only that all the questionnaires are filled out. Misclassification of non-differential information bias of the outcome can affect the results in both groups, but errors in outcome classification tend to be less common and have much less impact on the estimate of association. It tends to minimize any true difference between the groups (bias toward the null). Using stemless rather than stemmed prosthesis regarding revision surgery might have some advantages, but this study design does not allow us to investigate potential advantages or disadvantages; further studies must be carried out to address such issues.

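### Minor error: the total of 78 adds 20% instead of dividing by 0.8, so 20% loss leaves about 62 evaluable patients, not 64, and the abstract says eighty

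*Protocol article*

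**What the plan says.** All references are to the protocol article.

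- **Sample size and power calculation.** The inputs are given as "With an ACMC of 12.5% and a standard deviation (SD) of ±20.0", and the aim is "to be 80% sure that the lower limit of a one-sided 95% confidence interval will be above the non-inferiority threshold" of -12.5%. This leads to 64 patients, 32 in each group. The section continues: "With a loss of follow-up assumption of 20%, a total of 78 patients is required".
- **Discussion.** The allowance is said to have been made "by adding 20% to the sample size compensating for dropouts".
- **Material.** "Seventy-eight patients with shoulder osteoarthritis randomized to either stemmed or stemless shoulder prosthesis".
- **Trial status.** The recruitment target is again 78, and recruitment may be extended if it has not been met.
- **Abstract, Materials and methods.** The number to be randomly allocated is different: "Eighty patients with clinical and radiological signs of primary or post-traumatic glenohumeral osteoarthritis".
- **Data analysis.** Patients who drop out after the three-month visit stay in the analysis with their three-month value carried forward. Those who drop out earlier are left out unless they answer the one-year questionnaire.

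**The concern.** Two things do not fit. First, if 64 patients must remain after one in five is lost, the number randomized has to be 64 divided by 0.8. Adding 20% to 64 is a different operation and always falls short, because the loss applies to the larger, inflated number. Second, the article gives two current figures for how many patients will be randomized, eighty in the abstract and 78 in three sections of the body, and does not explain the difference.

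The figure is operational: Trial status uses 78 as the number that recruitment must reach. It is also the figure against which the final report will be compared. At stake are the stated combination of 80% power and 20% loss, and a reader's ability to tell which target the trial is working to.

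**Working it through.** **Inputs.** Study design states a "non-inferiority, randomized controlled clinical trial". From Sample size and power calculation: margin 12.5 percentage points of WOOS (237.5 of 1900), SD 20.0, one-sided 5% level, 80% power, 20% loss. Allocation is to two equal groups (Randomization and concealment of allocation). The article gives no value for the true difference between the groups. I assume 0, which reproduces the stated size.

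**Step 1: the evaluable number.**

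n per group = 2 x [SD x (z0.95 + z0.80) / margin]^2 = 2 x [20 x (1.645 + 0.842) / 12.5]^2 = 31.65, rounded up to 32.

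The total is 64, exactly as stated.

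**Step 2: how 78 arises.**

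- Adding 20% to the total: 64 x 1.2 = 76.8, rounded up to 77. This does not match.
- Adding 20% to each arm: 32 x 1.2 = 38.4, rounded up to 39; 2 x 39 = 78. This matches exactly.

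The article does not print this step, but it agrees with the Discussion's account of the allowance.

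**Step 3: what a 20% loss requires.**

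- 64 / (1 - 0.20) = 80, or 40 per group. Check: 80 x 0.80 = 64.
- Equivalently, 80 / 64 = 1.25, so a 20% loss calls for 25% more patients, not 20% more.

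**Step 4: what 78 delivers.**

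- 78 x 0.80 = 62.4, about 31 per group, which is 1 to 2 patients short of 64.
- The largest loss that still leaves 64 of 78 is 1 - 64/78 = 17.9%.

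**Step 5: power.** By the normal approximation, power = Phi[margin / (SD x sqrt(2/n)) - 1.645].

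- n = 32: 12.5 / (20 x 0.250) = 2.500; 2.500 - 1.645 = 0.855; power 80.4%.
- n = 31: 12.5 / (20 x 0.254) = 2.461; 2.461 - 1.645 = 0.816; power 79.3%.

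| Evaluable per group | Power, normal | Power, noncentral t |
|---|---|---|
| 32 | 80.4% | 79.6% |
| 31 | 79.3% | 78.5% |

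The difference is about one percentage point on either basis.

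**Step 6: the stated totals side by side.**

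| Section | Number randomized |
|---|---|
| Abstract, Materials and methods | 80 |
| Material | 78 |
| Sample size and power calculation | 78 |
| Trial status | 78 |

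**The case against.** The strongest reply is that this is two patients and makes no practical difference. Much of that stands. Going from 32 to 31 per group has the same effect on power as an SD of 20 x sqrt(32/31) = 20.3 in place of 20.0, and the SD is itself an estimate from a retrospective evaluation in one department. An SD of 20.5 with 32 per group would give about 78.6% by the normal approximation, a larger drop than the one at issue. By the t distribution, even 32 per group is slightly below 80%.

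A second reply is that 78 follows from the method the authors describe, so it is not a slip in calculation. That is right as far as it goes. The fault is in the method: adding 20% does not protect against a 20% loss.

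A third reply is that carry-forward keeps patients who drop out after three months, so the number analysed need not fall to 62. That is fair, and 62 is what remains only if the whole 20% leaves the analysis. It does not make 78 correct, however. The sample size section states its allowance without relying on carry-forward, and dropouts before three months are still excluded unless they answer at one year. The planned per-protocol analysis could also remove patients, by a number the article does not give.

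Two stronger readings are tempting. A reader might infer that the trial will miss its own size or is underpowered in a way that matters. The documents do not support this: 78 is the stated target in every section of the body that gives one, recruitment may be extended to reach it, and the power cost is about one point. A reader might also infer that the abstract's eighty is the correctly derived figure. It equals 64/0.8, but the abstract gives no derivation, and it could as well be a rounded number.

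**Conclusion.** Wrong as written, and minor. The total of 78 does not follow from 64 evaluable patients and a 20% loss, and it disagrees with the abstract. At the full 20% loss it leaves about 62 evaluable patients, with power about 79.3% (normal) or 78.5% (t), against 80.4% or 79.6% at 64. The figures assume a true difference of 0, an SD of 20 and a one-sided 5% level. The division by 0.8 and the conflict between 78 and eighty depend on none of these. The point concerns a wrong derivation and two conflicting targets; it does not call the trial's ability to answer its question into doubt.

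**What to change.** Use one number throughout the article. Two routes are open:

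1. **Keep 78.** Change the abstract to 78. In Sample size and power calculation, restate the allowance as about 18% loss to follow-up, or keep 20% and state the power as about 79%.
2. **Use 80, if that is the intended target as the abstract says.** State 80 (40 per group) in Material, Sample size and power calculation, and Trial status.

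On either route, correct the sentence in the Discussion about adding 20%, so that it gives the loss actually covered and, if 80 is used, says that the evaluable number was divided by 0.8.

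The first route costs only wording. The second costs wording and two more patients than the body of the article now plans.

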### Hypotheses

We hypothesize the following:A one-year postoperative WOOS score for patients operated with stemless TSA is inferior to that of patients operated with stemmed TSA by at least ACMC = 237.5 (12.5%).

$$ \left({\mathrm{H}}_0:{\upmu}_{\mathrm{stemmed}}>{\upmu}_{\mathrm{stemless}}+\mathrm{ACMC}\right) $$
A one-year postoperative WOOS score for patients operated with stemless TSA is not inferior to that of patients operated with stemmed TSA by ACMC = 237.5 (12.5%).

$$ \left({\mathrm{H}}_{\mathrm{A}}:{\upmu}_{\mathrm{stemmed}}\le {\upmu}_{\mathrm{stemless}}+\mathrm{ACMC}\right) $$

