## Outcome assessment tools

### Western Ontario Osteoarthritis of the Shoulder Score (WOOS)

The WOOS is a patient-administered, disease-specific questionnaire for the measurement of the quality of life of patients with osteoarthritis. It provides scores for four domains: (1) physical symptoms; (2) sport, recreation, and work; (3) lifestyle; and (4) emotions. Patients answer each question using the visual analogue scale. The WOOS score is calculated by measuring the distance from the left side of the line and calculating the possible score in the range of 0–100 (recorded to the nearest 0.5 mm.) It consists of 19 questions; the total score is in the range of 0–1900. A maximum score of 1900 signifies that the patient has an extreme decrease in shoulder-related quality of life, whereas a score of 0 signifies that the patient has no decrease in shoulder-related quality of life. The raw scores are converted to a percentage of the maximum score for simplicity of presentation. The questionnaire has been translated into Danish and validated and tested on patients with shoulder osteoarthritis [15, 18, 19].

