### Oxford Shoulder Score (OSS)

The OSS is a measurement tool for the assessment of outcomes of shoulder surgery [16, 20]. It has been tested and validated in patients with primary or secondary osteoarthritis. The OSS is a 12-item questionnaire, with each item scored in the range of 0–4; thus, the overall score is the sum of the scores received for individual questions. This results in a continuous score ranging from 0 (most severe symptoms) to 48 (least severe symptoms) [16]. For simplicity of presentation, the raw scores will be converted to a percentage of the maximum score. We will use a validated Danish version [20].

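### The non-inferiority hypotheses and the −12.5% lower-limit rule treat a higher WOOS as better, but the WOOS is defined with 0 as best and 1900 as worst

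*Protocol article*

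**What the plan says.** All places are in the protocol article.

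- **Western Ontario Osteoarthritis of the Shoulder Score (WOOS).** The top of the scale is the bad end: "A maximum score of 1900 signifies that the patient has an extreme decrease in shoulder-related quality of life". The bottom is the good end: "a score of 0 signifies that the patient has no decrease in shoulder-related quality of life". The percentage scale is then introduced with "The raw scores are converted to a percentage of the maximum score for simplicity of presentation". No reversal is mentioned here or anywhere else.
- **Sample size and power calculation.** The margin is 237.5 raw points, or 12.5% of the maximum. The aim is 80% power that "the lower limit of a one-sided 95% confidence interval will be above the non-inferiority threshold" of −12.5%. The order of subtraction is not given.
- **Hypotheses.** In words, the null is "A one-year postoperative WOOS score for patients operated with stemless TSA is inferior to that of patients operated with stemmed TSA by at least" the margin, and the alternative is that stemless is not inferior by that margin. The formulas beneath are H0: μ_stemmed > μ_stemless + ACMC and HA: μ_stemmed ≤ μ_stemless + ACMC, with ACMC = 237.5.
- **Oxford Shoulder Score (OSS).** The instrument from which the margin is extrapolated runs the other way, with 48 as best. It is converted to a percentage of its maximum in nearly the same terms.

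**The concern.** The words of the null hypothesis and its formula disagree once the formula is read on the score as the article defines it. A stemmed mean exceeding the stemless mean by more than 237.5 points means that the stemmed patients are worse off. Rejecting that null shows only that stemless is not better by more than the margin. It does not show that stemless is no worse than stemmed by the margin.

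This is the decision rule for the primary outcome. The low probability of declaring non-inferiority when the new implant is worse by the margin is the main protection in a non-inferiority trial. A reversed sign removes it, and it also withholds the claim when the new implant is clearly better.

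**Working it through.** **Inputs**

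- Margin 12.5 percentage points (0.125 × 1900 = 237.5 raw points): Sample size and power calculation.
- "a standard deviation (SD) of ±20.0": same section. No unit is attached. I read it as percentage points, which is 0.20 × 1900 = 380 raw points.
- 32 evaluable patients per arm, one-sided 95% limit, 80% power: same section.
- Score direction, 0 best and 1900 worst: WOOS section.

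**The article's own sample size**

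n per arm = 2 × SD² × (z₀.₉₅ + z₀.₈₀)² / margin² = 2 × 400 × (1.645 + 0.842)² / 156.25 ≈ 31.7, rounded up to 32 per arm and 64 in total. This reproduces the stated figure. The raw scale (margin 237.5, SD 380) gives the same 32.

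**Direction of the formulas**

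1. HA is μ_stemmed ≤ μ_stemless + ACMC. Rearranged, it is μ_stemless − μ_stemmed ≥ −ACMC.
2. This corresponds to requiring the lower limit of stemless minus stemmed to lie above −12.5%, so the sample-size rule and the formulas agree with each other under that order of subtraction.
3. Both are correct if a higher score is better. The WOOS section says that a higher score is worse, and raw/1900 keeps that direction.

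**Effect if the rule is applied to the score as defined**

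Let d be the true stemless minus stemmed difference in percentage points, with higher meaning worse.

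SE = 20 × √(2/32) = 5.

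- As written: P(declare non-inferior) = Φ((d + 12.5)/5 − 1.645). Success requires an observed difference above −12.5 + 1.645 × 5 ≈ −4.28.
- Matched to the definition (upper limit below +12.5): P = Φ((12.5 − d)/5 − 1.645). Success requires an observed difference below about +4.28.

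| True d | Meaning | As written | Matched to the definition |
|---|---|---|---|
| −25 | stemless much better | 0.002% | about 100% |
| −12.5 | stemless better by the margin | 5.0% | 99.96% |
| 0 | no difference | 80.4% | 80.4% |
| +12.5 | stemless worse by the margin | 99.96% | 5.0% |
| +25 | stemless much worse | about 100% | 0.002% |

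The key entry is d = +12.5: Φ(25/5 − 1.645) = Φ(3.355) = 0.9996. The two rules agree at d = 0, so the power calculation does not reveal the problem.

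**The case against.** The strongest reply is that a reversed score is meant and simply not described. The conversion sentence gives no formula and does not say which end is 100%. The verbal hypotheses state the right clinical intent, and the formulas and the −12.5% limit are both coherent for a score on which 100 is best. The margin in raw points does not rule this out, because 1900 − raw leaves the size of every difference unchanged. If the team analyses such a score, the analysis is sound and only the description is at fault.

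Second, the lower-limit rule taken alone is ambiguous rather than wrong. With the difference taken as stemmed minus stemless it would suit a lower-is-better scale.

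Third, the OSS direction is already stated, and two instruments running in opposite directions is not in itself an error.

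What stands of this: the verbal hypotheses are not wrong, the fault lies in the formulas set against the score definition, and the 99.96% is conditional on the rule being applied to unreversed scores. What does not stand is the idea that the text resolves itself. A percentage of the maximum, read plainly, is not a reversal, and nearly the same phrase is used for the OSS, where 48 is already the best score. Reading the limit rule as stemmed minus stemless would put it in conflict with the formulas. On every reading, at least one statement has to change.

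**Conclusion.** The concern holds. The primary hypotheses as written in symbols contradict the primary score as defined, and nothing else in the article repairs this. The lower-limit rule carries the same reversal under the only order of subtraction consistent with those formulas.

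Applied literally, with 32 per arm, SD 20 percentage points and a normal approximation, the chance of declaring non-inferiority when stemless is worse by the full margin is 99.96% instead of 5%. The chance when stemless is better by the margin is 5% instead of 99.96%. These figures describe the rule on the score as defined; they are not a forecast of what an analyst using a reversed score would do. The sample size, the size of the margin and the 80.4% power at no true difference do not change.

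Because the sign of the primary decision rule is at issue, this should be corrected before any comparison by arm is seen. Settled afterwards, it would look like a choice made on the results.

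**What to change.** Choose one of two equivalent repairs.

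1. **Reverse the score and keep the rule.** In the WOOS section, define the analysed score as WOOS% = 100 × (1900 − raw)/1900, so that 100 is best. State that the sample-size section and the hypotheses refer to this score, with the 237.5-point margin read on 1900 − raw.
2. **Keep the raw direction and reverse the rule.** Write H0: μ_stemless ≥ μ_stemmed + 237.5 and HA: μ_stemless < μ_stemmed + 237.5. Declare non-inferiority if the upper one-sided 95% limit of stemless minus stemmed lies below +12.5%.

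Under either option, state the order of subtraction next to the limit rule, and say once for WOOS and once for OSS which end of the reported percentage scale is better.

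The cost is protocol and SAP wording only. The sample size stays at 32 evaluable patients per arm, and data collection does not change.

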#### Data analysis

No interim data analysis will be carried out. The primary investigator will enter data in the REDCap database, and the principle investigator before the data analysis will perform proofreading of a random sample of 20 patients.

Data analysis will be conducted by a blinded biostatistician. Patients who drop out after the three-month evaluation will be included in the analysis based on three months of data (“last observation carried forward”). Patient dropouts before the three months’ evaluation will not be included in the analysis unless they participate in the one-year questionnaire evaluation. As suggested in the extension of the CONSORT statement for non-inferiority trial design, a per-protocol analysis will be conducted and results obtained [28, 29]. A questionnaire containing one or more missing answers will be marked as incomplete; the patients will be contacted by letter to answer the missing questions.

Descriptive statistics will be used to report demographic data. Differences in demographic data and outcome measures between the two groups will be compared using chi-square test for categorical variables; parametric (Student’s t-test) or non-parametric (Mann–Whitney U-test) test for continuous variables depending on the nature of data. Data will be checked for possible extreme values before the analysis. The statistical analyses will be performed using SPSS version 25.0 (IBM Corp, Armonk, NY, USA) [30]. The level of statistical significance is set at *P* < 0.05; all *P* values are two-tailed. All complications, including glenoid and humeral component loosening, glenoid wear instability, rotator cuff tear, intraoperative and postoperative periprosthetic fracture, nerve injury, infection, deltoid injury, and deep venous thrombosis will be reported. Our sample size does not give us enough power to allow comparison.

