## Outcome measures

The primary outcome will be the Western Ontario Osteoarthritis Shoulder (WOOS) score at 12 months [15].

The secondary outcomes will measure the following:WOOS score at three months;OSS at 3 and 12 months postoperatively [16];General health status questionnaire EQ-5D at 3 and 12 months [17].

At baseline, three-, and twelve-month visits, patients will fill out questionnaires, WOOS, OSS, and EQ-5D, alone before leaving the hospital (at the second visit after accepting participation) and in the waiting room (at three- and twelve-month visits) without interference from the medical staff.

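### Using the 3-month WOOS in place of a missing 12-month WOOS can bias the non-inferiority test, in a direction and by an amount the protocol's figures cannot bound

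*Protocol article*

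**What the plan says.** The Study design section describes a "non-inferiority, randomized controlled clinical trial". Under Outcome measures, "The primary outcome will be the Western Ontario Osteoarthritis Shoulder (WOOS) score at 12 months", and "WOOS score at three months" is listed separately as a secondary outcome. The Hypotheses section is likewise framed on the one-year score.

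The Data analysis section then fixes how dropout is handled. For later losses: "Patients who drop out after the three-month evaluation will be included in the analysis based on three months of data", which the protocol itself labels last observation carried forward (LOCF). For patients lost before the three-month visit, the rule is that those leaving before that "evaluation will not be included in the analysis unless they participate in the one-year questionnaire evaluation". The article names no other handling of missing scores.

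The Sample size section assumes 20% loss to follow-up in total. It does not divide that loss between arms, or between the periods before and after three months.

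**The concern.** The estimand is a 12-month difference, but for anyone lost between months 3 and 12 the analysed value is a 3-month score, with no stated allowance for its being imputed. Three months is early in recovery: the rehabilitation section restricts some movements until six weeks.

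Two things can go wrong. If the difference between implants at 3 months is not the same as at 12 months, the carried-forward patients move the estimate toward the 3-month difference. If scores are still improving after 3 months and the arms lose different proportions, the arm that loses more is held back.

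In a non-inferiority trial any movement of the estimate in favour of the stemless implant makes a false claim more likely. At stake is whether the 5% one-sided error that underlies the sample size is the error the trial will actually run.

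**Working it through.** **Inputs from the protocol.** Margin 12.5 percentage points; "a standard deviation (SD) of ±20.0"; one-sided 95% limit; 80% power; 32 per arm before loss; 20% loss; 78 in total, so 39 per arm.

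**The plan's own figure.** n per arm = 2 × [20 × (1.645 + 0.842) / 12.5]² = 31.65, rounded up to 32, or 64 in total. Adding 20%: 32 × 1.2 = 38.4, rounded up to 39 per arm, or 78. The stated sample size reproduces and this point does not affect it.

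**Assumptions not in the protocol.** A gain of 15 points from 3 to 12 months, a correlation of 0.5 between the two visits, dropout unrelated to outcome, and several values for the 3-month difference and for the share carried forward.

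**Expected estimate under LOCF.** Take the difference as stemless minus stemmed, with higher meaning better, as the hypotheses do. Let d12 and d3 be the true 12- and 3-month differences, g the gain in the stemmed arm, and fₛ (stemless) and f꜀ (stemmed) the shares carried forward. Then

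E = d12 + fₛ × (d3 − d12) + g × (f꜀ − fₛ).

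Set d12 = −12.5, the margin, where the chance of claiming non-inferiority should be 5%.

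- 20% in each arm, d3 = 0: −12.5 + 0.2 × 12.5 = −10.0.
- 10% in each arm, d3 = 0: −12.5 + 0.1 × 12.5 = −11.25.
- 20% in each arm, d3 = −6.25: −12.5 + 0.2 × 6.25 = −11.25.
- Equal shares, d3 = −12.5: no shift.
- 10% stemless, 20% stemmed, d3 = −12.5: −12.5 + 15 × 0.1 = −11.0.
- 20% stemless, 10% stemmed, d3 = −12.5: −12.5 − 15 × 0.1 = −14.0.

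**Hand check of the error rate.** The standard error is 20 × √(2/39) = 4.53. A shift of b points gives P(Z > 1.645 − b/4.53). For b = 2.5 this is P(Z > 1.093), about 13.7%. For b = 1.25 it is P(Z > 1.369), about 8.6%. For b = 1.5 it is P(Z > 1.314), about 9.4%. For b = −1.5 it is P(Z > 1.976), about 2.4%.

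**Simulation.** The simulation used a pooled t interval and a one-sided 95% limit against −12.5. It allows for the extra spread from mixing 3- and 12-month scores, which the hand check ignores.

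| Carried forward (stemless / stemmed) | 3-month difference | False non-inferiority |
|---|---|---|
| 10% / 10% | 0 | about 8% |
| 20% / 20% | 0 | about 13% |
| 20% / 20% | −6.25 | about 8% |
| 20% / 20% | −12.5 | about 5% |
| 20% / 20% | −18 | about 3% |
| 10% / 20% | −12.5 | about 8–9% |
| 20% / 10% | −12.5 | about 2–3% |

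With equal shares the gain hardly matters: varying it from 0 to 20 points leaves the 20%, d3 = 0 case at 13.0–13.5%.

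**Reference.** Using only observed 12-month scores, with dropout unrelated to outcome, the error is 5.1% at 20% loss in both arms and 4.9% at 10% stemless / 30% stemmed. Under those conditions the distortion comes from the LOCF rule, not from the loss itself.

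**The case against.** The strongest reply is that inflation is not automatic. It disappears when the 3-month difference equals the 12-month difference and dropout is equal. It reverses when the 3-month difference is larger, and generally when more stemless patients are lost. The documents give no 3-month mean, no 3-month difference and no dropout by arm. All of this stands, so a reader who infers that LOCF necessarily inflates false claims here goes further than the protocol allows.

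Four other stronger readings also fail.

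- The 20% cannot be read as the share carried forward. It is the total assumed loss and includes patients lost before 3 months, so the 13% is an upper case. Planned telephone contact with non-attenders may lower it further.
- Excluding early losses does not by itself pull the arms together. It biases the result only if loss is related to outcome, on which the article gives nothing, and those who answer the one-year questionnaire are readmitted.
- The Discussion's remark "It tends to minimize any true difference between the groups (bias toward the null" might be taken as reassurance about dropout. It concerns non-differential misclassification of the outcome, so it is not evidence on this point.
- One might infer that late implant failures would be hidden. A patient with a failure who completes the 12-month questionnaire contributes that score, and complications are recorded separately. Only the mean WOOS misses a failure, and only if the patient is also lost; the calculations do not test this.

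Sensitivity analyses may also sit in a statistical analysis plan that is not shown, so their absence from the article is not a fault. None of this rescues the stated rule: it is a fixed choice, and its error rate depends on quantities that the protocol does not constrain.

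**Conclusion.** The point holds in conditional form. The protocol substitutes a secondary time point for the primary one in patients lost after 3 months, and the error of the non-inferiority test is then no longer tied to 5%. Over the scenarios tabulated it runs from about 2–3% to about 13%. The upper end requires no difference at 3 months, a full-margin difference at 12 months and all of the planned 20% loss falling after 3 months. With 10% carried forward and no 3-month difference the figure is about 8%.

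These sizes rest on the assumed 15-point gain, the correlation of 0.5 and dropout unrelated to outcome. The direction cannot be settled from the documents. The rule should still be changed, because the trial could not show that its stated error is maintained and the data for a better analysis are already being collected.

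**What to change.** Remove LOCF as the primary rule and keep it at most as a sensitivity analysis. Estimate the 12-month contrast in one of two ways:

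- a likelihood-based repeated-measures model of baseline, 3- and 12-month WOOS; or
- multiple imputation of the 12-month score from arm, baseline and 3-month WOOS.

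Either uses the 3-month score as information about month 12 rather than as a substitute for it, and lets patients lost before 3 months contribute what they have. Both assume that, given the observed scores, loss is unrelated to the unseen 12-month score. So add a tipping-point sensitivity analysis that lowers the missing stemless scores by increasing amounts and reports where the conclusion changes.

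The cost is a change of wording and slightly more analysis work. No new data are needed, since WOOS is already collected at all three visits, and the sample-size calculation is untouched.
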